**Figure 4 F4:**
[figure not shown]
Recruitment and flow of patients (projected).

### Primary outcome measure

The primary outcome measure of the SMADS-study is self-efficacy. This measure will be assessed by the General Self-Efficacy Scale (GSE-Scale), [25].

Perceived self efficacy is an important prerequisite for successful self-management [26]. The construct, theoretically and empirically [20] well founded, was originally developed by Albert Bandura in the 1970s. Bandura defines self-efficacy as “people’s beliefs about their capabilities to produce designated levels of performance that exercise influence over events that affect their lives” [27]. Based on improved self-efficacy patients can regain control of their own lives, gaining new confidence in their ability to perform a task. Yet, as Battersby et al. wrote, “self-efficacy is not a process; it is an intermediate outcome or mediator of a patient’s adoption of self-management behaviours and health behaviour changes” [28].

The GSE-questionnaire operationalizes the psychological construct „self efficacy“, consisting of 10 items ranging from 1 = Not at all true, 2 = Hardly true, 3 = Moderately true to 4 = Exactly true. The GSE is a valid, theoretically driven, globally used measurement for the assessment of self-efficacy and has been translated into 31 languages. The scale measures a general sense of perceived self-efficacy. It predicts the ability to cope with everyday life, as well as the ability to adapt after experiencing all kinds of stressful life events [29].

### Study hypotheses

We hypothesize, the APN will improve the self-efficacy expectations of the patients in the intervention group by about 2.7 points assuming a common standard deviation of 5.4 points. A significant increase in this measure indicates a better ability to perform the broad range of self-management techniques. A patient who is more convinced of his or her own chance to have impact on one’s own life is better prepared to build up resilience against stressors in life.

### Secondary outcome measures

As secondary outcome measures we assess the symptom load using the PHQ-D. The PHQ-D is a well established instrument to screen patients for anxious, depressive and somatoform symptoms. It has good validity and prognostic capabilities [24]. We decided against the use of the PHQ-D as the primary outcome, even though we use it as a screening tool to include patients. This is justified by the supreme goal of the study: Supporting self-management, measured indirectly, using self-efficacy as a proxy.

In addition, patients will be assessed on their health related quality of life, answering the EQ-5D questionnaire. The EQ-5D, a 5-item-questionnaire, developed by the EuroQoL-group (http://www.euroqol.org), is comprised of five dimensions: mobility, self-care, usual activities, pain/discomfort and anxiety/depression. A visual analogue scale evaluates the patients self-rated health on a vertical scale where the endpoints are labeled ‘100 - Best imaginable health state’ and ‘0 - Worst imaginable health state’. The EQ-5D has satisfying psychometric properties. There are published reference values for the general population [30]. Furthermore, coping will be assessed with the “Coping with Illness scale” [31]. It assesses a broad range of cognitive, behavioural and emotional aspects of coping with an illness. Investigators use the short version.

Further evaluations include the analyses of cost-effectiveness, the subsequent number of sickness leaves, and the utilization of the health care system in the year post-baseline.

### Statistical analyses

For the primary outcome we evaluate the changes in comparison to the baseline GSE after 12 months. A linear mixed model will be calculated for the difference between the intervention and control groups. The variable “group” will be considered a fixed effect while the practice will be considered a random effect under the control of the baseline covariates (baseline values of GSE and other confounders like PHQ-D, age, gender, education, utilization of the health care system on patient level, as well as age, gender, status of practice (single or group) on practice level. The two-sided α-level was set to 0.05.

The analyses of the primary outcome will be based on an intention-to-treat-(ITT)-analysis: All patients enrolled into the study will be analyzed at follow-up. All drop-outs not having withdrawn their consent will be asked again to take part in the final assessment 12-months-post-baseline. If patients reject this invitation or cannot be reached at all, their values will be imputed using the last-observation carried forward (LOCF) method.

The robustness of the results will be investigated performing sensitivity analyses with different methods of imputing missing values.

The same procedures will be applied for the PHQ-D, the EQ-5D and the „Coping with Illness scale“ as secondary outcomes. There will also be analyses of the observed cases (OC). These analyses will include only those patients, who did not drop out and completed the final assessment.

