## Methods

### Study design

We set up an open label, cluster-randomized controlled trial. We randomly allocate participating general practices to either the interventional arm, in which a nurse-led collaborative care model is implemented, or to the control arm in which the GP continues his/her usual routine care treating ADSom-patients.

The APN will work directly in the primary care practices. All participants will be assessed at baseline, 8 weeks post-baseline and 12 months post-baseline. The scheduled time for providing services in the interventional primary care practices is 12 months. In the control practices, the patients obtain the „usual care“ by the GP. In this arm, the course of the disease and the utilization of GPs or other professions will be documented. The interventions will take place in the general practices, the APNs having an own office at their disposal. The practice and the APN arrange a fixed weekday on which the nurses work in this particular practice. Figure 1 illustrates patient flow of the SMADS-study.

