### Handling of dropouts

We are accounting for 2 different groups of dropouts:

• Patients declaring to abandon the intervention or repeatedly missing appointments, and

• Patients cancelling their consent, thus, withdraw from the study.

All dropouts, who will not withdraw their consent will be contacted again 12 months post-baseline to get a chance to answer the study questionnaire. Dropouts are accounted for in the intention-to-treat-analyses.

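### The observed-cases set drops patients whose 12-month value was observed, by a rule that depends partly on the arm

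*Protocol article*

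**What the plan says.** All references are to the protocol article.

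- **Statistical analyses, OC set.** After the primary and secondary outcomes, the section adds OC analyses and defines their population: "These analyses will include only those patients, who did not drop out and completed the final assessment". These are two conditions, and both must hold.
- **Handling of dropouts, definition.** There are two groups. The first is "Patients declaring to abandon the intervention or repeatedly missing appointments". The second is "Patients cancelling their consent, thus, withdraw from the study".
- **Handling of dropouts, follow-up.** "All dropouts, who will not withdraw their consent will be contacted again 12 months post-baseline to get a chance to answer the study questionnaire". The Statistical analyses section says the same in other words.
- **Study design, control arm.** "In the control practices, the patients obtain the „usual care“ by the GP".
- **Statistical analyses, primary set.** The primary analysis is by intention to treat: "All patients enrolled into the study will be analyzed at follow-up". Last observation carried forward is used only for patients who refuse the 12-month invitation or cannot be reached.

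**The concern.** The first drop-out group is defined by what patients do about treatment, not by whether their outcome is missing. The plan then goes back to these patients for the 12-month questionnaire, so it expects some of them to have an observed outcome. The OC rule removes them all the same, because they fail its first condition. A set named for observed cases thus leaves out observed cases.

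The removal is not symmetric. Usual-care patients have no nurse intervention to abandon, so that criterion can take patients only from the intervention arm. The OC contrast then sets intervention patients who stayed in treatment against control patients who were never put to that test, and randomisation of practices no longer protects it.

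At stake is what the OC result can tell a reader. With a simple definition, OC and intention-to-treat would differ only in the imputed values, and the comparison would show how much the carried-forward values matter. As written, two things change at once: imputation is removed, and so are patients who left treatment. Agreement or disagreement between the two analyses then has no clear meaning.

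**Working it through.** **1. The plan's own figures, as a check on the inputs.** From Sample size/power calculation: difference 2.7, SD 5.4, intra-cluster correlation 0.05, power 80%, 20 clusters of 11, drop-out 33%, 340 recruited. Two-sided α of 0.05 is from Statistical analyses.

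- Individually randomised n per arm: 2 × (1.96 + 0.84)² × (5.4/2.7)² = 62.8, so 63.
- Design effect: 1 + (11 − 1) × 0.05 = 1.5.
- Clusters per arm: 62.8 × 1.5 / 11 = 8.56. Adding one per arm for the small number of clusters gives 9.56, so 10, and 20 × 11 = 220.
- Power at 10 × 11 per arm: 81.7% (noncentral t, 18 df).
- Drop-out: 11 / 0.67 = 16.4, so 17 per cluster, and 17 × 20 = 340.

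The sample size reproduces and is not in dispute.

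**2. The definitions side by side.**

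| Patient | Drop-out? | 12-month value possible? | In OC as written? | Which arm? |
|---|---|---|---|---|
| Abandoned the intervention, answers on recontact | yes | yes | no | intervention only |
| Repeatedly missed appointments, answers on recontact | yes | yes | no | not stated |
| Withdrew consent | yes | no (not recontacted) | no | either |
| Not a drop-out, questionnaire completed | no | yes | yes | either |

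The first two rows are the problem: the outcome is observed, yet the patient is left out.

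**3. Size of the bias.** Take the intervention patients with a 12-month value. Let q be the share removed as drop-outs, and g the amount by which their mean GSE result, after adjustment, falls below that of the patients kept. If those kept have mean K:

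- mean of all observed = (1 − q)K + q(K − g) = K − qg;
- mean of the OC set = K;
- shift in the intervention mean, and so in the contrast when no control patients are removed = q × g.

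The article gives neither q nor g. Both are assumptions here. Results are in GSE points, with the percentage of the 2.7-point target in brackets:

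| q | g = −2.7 | g = 0 | g = 1.35 | g = 2.7 | g = 5.4 |
|---|---|---|---|---|---|
| 0.05 | −0.14 (−5%) | 0 | 0.07 (2%) | 0.14 (5%) | 0.27 (10%) |
| 0.10 | −0.27 (−10%) | 0 | 0.14 (5%) | 0.27 (10%) | 0.54 (20%) |
| 0.20 | −0.54 (−20%) | 0 | 0.27 (10%) | 0.54 (20%) | 1.08 (40%) |

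**4. Effect on the OC test when there is no true effect.** Start from 11 observed patients per cluster and remove a share q in the intervention arm only. Then SE = 5.4 × √[D/(110(1 − q)) + 1.5/110], with D = 1 + (11(1 − q) − 1) × 0.05. For g = 2.7:

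- q = 0.10: D = 1.445, SE = 0.907, shift 0.27; two-sided rejection about 6%.
- q = 0.20: D = 1.39, SE = 0.926, shift 0.54; two-sided rejection about 9%.

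Both use a noncentral t with 18 df and are not adjusted for covariates.

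**5. Under a definition that asks only for a completed 12-month assessment,** q = 0 and this bias term is zero.

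**The case against.** The strongest defence is that OC is a supplementary analysis. The primary analysis keeps every enrolled patient and uses recontacted 12-month values where they exist, so the trial does not waste the data it went back for. Robustness is assigned to separate sensitivity analyses with other imputation methods. OC is added after the sentence on secondary outcomes, and it is not clear that it covers the GSE at all. This stands, and it confines the point to the OC analyses.

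A milder reading is also possible: not having dropped out may simply mean having a 12-month value. But the first condition would then repeat the second, and the term would carry a different meaning from the one in Handling of dropouts. The two sections need reconciling on either reading.

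A reader might infer more than the article supports:

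- **That the exclusion can happen only in the intervention arm.** This is certain for abandoning the intervention. For missed appointments it is not, since the article does not say which appointments are meant and both arms are assessed on the same schedule. Consent withdrawal can occur in either arm.
- **That the bias favours the intervention.** This is plausible if those who leave do worse, but nothing in the article shows that they do. Entry is deliberately low-threshold, and some may stop because they have improved.
- **That a third of the arm is affected.** The 33% is the planned loss between 340 recruited and 220 analysed. It is not the share who leave treatment and then return the questionnaire, for which no figure is given.

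Finally, the planned adjustment for baseline GSE, PHQ-D and other covariates may absorb part of any gap. That is why g is defined above as what remains after adjustment.

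**Conclusion.** The point holds for the OC analyses. Under the stated definitions they exclude patients with observed 12-month outcomes. One of the exclusion criteria exists in one arm only, so the set is closer to per-protocol than to observed cases.

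The OC contrast is open to a bias of q × g whose sign and size the article does not determine. With q between 0.05 and 0.20 and g = 2.7 as assumptions, it is about 0.14 to 0.54 GSE points, or 5% to 20% of the target difference. It is zero if those removed do not differ, and it runs against the intervention if they do better. These figures also assume that no control patients are removed under the missed-appointments criterion.

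It would be wrong to conclude that the primary result is biased. The intention-to-treat analysis does not use this exclusion.

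**What to change.** Replace the OC definition with one sentence: the observed-cases set is every enrolled patient in either arm with a completed 12-month assessment, whatever their attendance or drop-out status. If an analysis without those who abandoned the intervention is also wanted, label it per-protocol.

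It would help to state which appointments the drop-out definition refers to, and to report by arm how many drop-outs supplied a 12-month questionnaire on recontact, so that q is known.

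The cost is a small edit to the text. No new data, patients or assessments are needed, and the primary analysis and sample size stay as they are.

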### Handling of dropouts

We are accounting for 2 different groups of dropouts:

• Patients declaring to abandon the intervention or repeatedly missing appointments, and

• Patients cancelling their consent, thus, withdraw from the study.

All dropouts, who will not withdraw their consent will be contacted again 12 months post-baseline to get a chance to answer the study questionnaire. Dropouts are accounted for in the intention-to-treat-analyses.

### Methods against bias

Selection bias will be minimized by the randomization of the practices. The standard recruiting procedure (establishing a screening day in the practice) also tries to keep the selection bias checked. In order to collect the required data for a CONSORT flow chart (for clustered trials), the full recruitment process will be documented.

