### Study population and recruitment

The study is conducted in the city of Hamburg. Citywide, half of the GPs are asked to participate. Additionally, we will recruit GPs by introducing the project in quality circles and contacting the Hamburg Association of General Practitioners. As we build up the APN staff step by step we include practices in a similar mode. The process of recruiting practices is ongoing.

Inclusion criteria for practices are:

• Willingness to participate in the study regardless of randomization to the intervention or control arm,

• One single private room at scheduled times for the APN to deliver the intervention in a protected environment,

• No psychotherapeutic treatment within the practice, neither by the GP him/herself nor by any other professional in the practice,

• No participation in other studies of “Psychenet: Hamburg Network for Mental Health”.

The patient recruitment is based on an assessment taking place in the practice on a particular screening day. As the capacity of the APN is limited, and we don’t want to create waiting lists, it is required to recruit patients into the study adjusted to the APN’s treating capacity.

The first part of the assessment is done by the GP: All patients who are seen by the doctor on the screening day, will be put on a chart and checked for inclusion criteria.

Eligibility criteria for patients are:

1) PHQ ≥ 5 on the anxiety, depression or somatoform scale,

2) Age: 18–65 years old,

3) Literacy (German),

4) Fully able to give consent,

5) Sufficient auditory and visual capabilities,

6) Currently no psychotherapeutic treatment.

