### PHQ-D-assessment

Patients found eligible will be informed about the study. The patient will receive written and verbal information from the GP. The information covers the aims and procedures of the study, the selection of participants, the data collection, processing and storage, as well as possibilities for cancellation. In case these terms are accepted, the participants will have to sign an informed consent form to participate in the study. Besides that, patients have to agree to release their physician of his/her medical confidentiality allowing the APN and the GP to exchange information. Patients will be asked to complete the “Patient Health Questionnaire-D (PHQ-D)” [24] and other instruments introduced later in this paper.

The target population for the intervention are adults aged 18 to 65 scoring ≥5 on any of the three symptom scales that are incorporated in the PHQ-D: Anxiety, using the seven items of the General Anxiety Disorder-Scale (GAD-7); Depression, using the nine items of the PHQ-9 depression scale; or somatoform symptoms which are checked by the fifteen-item somatization scale of the PHQ, PHQ-15.

Psychiatric symptoms fluctuate on a daily basis and overlap between the disorders [8]. Thus, we expect many patients to score above the cut-off on any of the scales. A score as low as ≥5 to gain access to the counseling service in the GP practice emphasizes the low-threshold approach of the intervention. When considering prevention, early support may impede a chronic condition later on.

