### Detection bias

Practices in the control arm will have the chance to employ an APN after finishing the randomized controlled trial in order to avoid a possible lack of motivation for recruitment and documentation. The APNs will be working in these practices for another 12 months. Furthermore, control practices will get the same financial compensation for their engagement as the GPs in the intervention arm.

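### Randomising practices does not, as claimed, minimise selection bias among patients whom GPs enrol after allocation in an open-label trial

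*Protocol article*

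**What the plan says.** All references are to the protocol article.

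- **Methods against bias** names practice randomisation as the main protection: "Selection bias will be minimized by the randomization of the practices". It adds a second: "The standard recruiting procedure (establishing a screening day in the practice) also tries to keep the selection bias checked". It also promises to document the whole recruitment process for a cluster-trial flow chart.
- **Study design**: "We set up an open label, cluster-randomized controlled trial".
- **Study population and recruitment**: "The first part of the assessment is done by the GP", and "All patients who are seen by the doctor on the screening day, will be put on a chart and checked for inclusion criteria". Because nurse time is limited and waiting lists are unwanted, "it is required to recruit patients into the study adjusted to the APN’s treating capacity".
- **PHQ-D-assessment**: "Patients found eligible will be informed about the study". The GP gives the written and verbal information, the patient signs, and the PHQ-D is described after that. A score of 5 or more on any of three scales defines the target population.
- **Detection bias**: control practices may have an APN once the trial is over, and receive the same payment as intervention practices. The stated purpose of the later APN is "in order to avoid a possible lack of motivation for recruitment and documentation".
- **Statistical analyses**: the mixed model adjusts for baseline GSE, PHQ-D, age, gender, education and health care utilisation, and for practice-level covariates.

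**The concern.** In a cluster trial there are two points at which selection can occur: which practices enter each arm, and which patients enter within each practice. Randomising practices deals with the first. It can deal with the second only if patients are identified and enrolled before the arm is known, or by someone who does not know it. The article describes neither arrangement, yet it credits randomisation with minimising selection bias in general.

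An intervention GP who knows that a nurse is available may present the study more warmly to patients thought likely to engage. A control GP has no such prompt. If the arms then differ in motivation or readiness for counselling, and these relate to self-efficacy at 12 months, the primary comparison mixes that difference with the treatment effect. Baseline adjustment covers only what was measured, and a larger sample does not shrink the bias.

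**Working it through.** **1. Is the arm known when patients are recruited?** The order of practice allocation and patient enrolment is not stated outright. The trial is open label, and the later APN offer to control practices is justified by a worry about their motivation to recruit. That worry makes sense only if they recruit knowing that they are controls. Arm knowledge at recruitment is therefore a well-supported inference.

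**2. Who stands between the arm and the patient?** The practice's own GP lists attenders, checks criteria and explains the study. Some exclusions (immobile patients, those who are not regulars) leave room for judgement. No recruiter blind to arm is described.

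**3. Is intake paced alike?** Recruitment is matched to APN capacity. Control practices have no APN until the trial ends, and no equivalent pacing rule is given for them. The text names no arm, so pacing may be equal or unequal.

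**4. What does each safeguard achieve?**
- The all-attender list fixes the sampling frame, but not how the study is presented or who agrees.
- The PHQ threshold keeps out patients below the cut-off, but does not balance those above it.
- Documented recruitment exposes an imbalance without preventing it.
- Covariate adjustment handles the listed variables only.

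**5. How much could a residual bias matter?** Inputs from Sample size/power calculation: difference 2.7, SD 5.4, ICC 0.05, 20 clusters of 11 (220 analysed, 110 per arm). The two-sided 5% level is from Statistical analyses.

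- Design effect = 1 + (11 − 1) × 0.05 = 1.5.
- SE of the difference = 5.4 × √(2 × 1.5 / 110) = 0.892 points.
- The plan's own figure: noncentrality 2.7 / 0.892 = 3.03. A t-test on 20 − 2 = 18 degrees of freedom has 81.7% power, and clusters of 10 would give 79.3%. The stated 220 for 80% power is reproduced, so the sample size is not in question here.
- With no true effect and a residual selection bias b, the rejection probability is that of a noncentral t with 18 df and noncentrality b / 0.892.

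| Assumed bias b (points) | Share of 2.7 | Actual two-sided error rate |
|---|---|---|
| 0 | 0% | 5% |
| 0.27 | 10% | 5.9% |
| 0.5 | 19% | 8.3% |
| 0.81 | 30% | 13.8% |
| 1.0 | 37% | 18.6% |
| 1.35 | 50% | 30.0% |

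Every value of b is an assumption. One route to 0.5 points: 25% of one arm are selected differently and differ by 2 points after adjustment, so 0.25 × 2 = 0.5. Neither input comes from the article.

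**The case against.** The best defence is that the article does not rely on randomisation alone. The sentence after the claim names the screening day, on which every patient seen is listed and checked, and this limits hand-picking. The PHQ score still gates inclusion, and most other criteria (age, literacy, no current psychotherapy) are largely factual. Practices must accept either arm, payment is equal, the model adjusts for many covariates, and an article may leave recruitment details to the full protocol. All of this stands, and it makes gross steering less likely. It does not make the quoted sentence true, because none of these measures is randomisation and none conceals the arm from the person presenting the study.

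Three stronger readings are tempting and are not supported:

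- *Only intervention practices are limited by APN capacity.* No arm is named, and the planned 170 per arm, on average 17 per practice, is compatible with matched pacing.
- *The GP's judgement alone selects patients, because the PHQ-D comes after consent.* The article calls the PHQ-D its screening tool and defines the target population by the score. The order of the narrative is loose, but the threshold still applies.
- *Patients consent knowing which care they will receive.* This is plausible in an open-label trial, but the article does not say it.

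The error rates above show what a bias of a given size would do. They do not show that this trial has one, or in which direction.

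**Conclusion.** The claimed protection is wrong as written. Practice randomisation balances practices and does not guard against differential enrolment of patients after allocation. This conclusion rests on the open-label design, on the GP's role in screening and informing, and on the inference that control practices know their arm while recruiting. Unequal pacing by APN capacity is a further risk that the text leaves open.

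The size of any bias cannot be derived from the document. At the plan's SE of 0.89, an assumed residual bias of 0.5 or 1.0 GSE points would raise the false-positive rate from 5% to about 8% or 19%. The listed safeguards lower the chance of such a bias or make it visible, but do not remove differences in unmeasured factors. Recruitment can be improved cheaply, and the article says that recruitment of practices is still under way.

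**What to change.** 1. In Methods against bias, replace the claim with a statement that cluster randomisation does not prevent selection after allocation and that residual recruitment bias is possible despite the screening-day procedure.
2. State one intake rule for both arms: the same screening-day schedule, the same maximum intake, and eligible patients invited consecutively in arrival order. Any limit set by APN capacity then applies equally to control practices.
3. In practices not yet allocated, complete identification, consent and baseline assessment for the first screening day before the arm is released.
4. In the flow chart already planned, show the numbers screened, eligible, invited and consented by arm, and report baseline GSE and PHQ-D by arm alongside it.

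Cost: intake in control practices may be slower, and practices learn their arm a little later. The third step conceals the arm for first-day patients only, so later intake still depends on the common rule and on reporting. No additional participants are needed.
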